#### Feasibility and acceptability data

Data regarding feasibility and acceptability will be collected and reported at descriptive end. Those data will consist of recruitment rate, duration between each time of measurement and retention rate for each group. Moreover, participants will be contacted after their participation in the study to be interviewed and asked about the changes they observed in their symptoms and their point of view regarding the intervention.

### Intervention

All participants will be provided with a virtual reality headset with an integrated audio system. The Meta Quest Pro, released in 2022, will be used. A tablet connected to the headset will host the hypnosis application developed by Super Splendide (www.supersplendide.com), a company that specialises in the development of virtual reality applications. In collaboration with clinicians, researchers in the field of medical hypnosis and patient partners, Super Splendide is developing an intervention programme that combines VRH. The intervention will be delivered by one of the team members (research assistant adequately trained to communicate with participants, the intervention and the measurement tools) and supervised by VF (postdoctoral researcher in health psychology) and DO (senior researcher and clinical psychologist in pain clinics). Supervisors will be in charge of verifying the correct running of recruitments and data collection and will check those points once every 2 weeks.

For sessions 1 and 2 (ie, time 1 and time 2), participants from both the experimental and control group will not interact with the environment; they will simply be asked to watch and explore a 3D animation of a beach or a forest and relax during the session. The sounds may include the ocean, birds, wind, a crackling campfire and relaxing music. In the control group, sessions 3 and 4 (ie, time 3 and time 4) will consist of the repetition of sessions 1 and 2. In the experimental group, participants will be introduced to hypnosis techniques, the ‘magic hand’ intervention (ie, learning to apply analgesia with their hand) and to an intervention that involves manipulating their pain through an augmented reality script.

A counterbalancing procedure will be applied, respectively for sessions 1 and 2 (ie, beach or forest) and for sessions 3 and 4 (ie, magic hand or pain manipulation).

The fifth session (ie, time 5, follow-up) will correspond to a repetition of the first session (ie, time 1), the aim being to collect data in the exact same conditions to compare baseline and data collected after the intervention.

Given that cybersickness (ie, symptoms occurring when people are exposed to virtual reality) could occur, this variable will be systematically controlled for after each session in all participants with a dedicated questionnaire.^61^

### Data collection

Consent, questionnaire data and sociodemographic information will be provided by participants on a tablet using the software REDCap. The tablet will be provided by the research assistant in charge of data collection.

Participants will be included prospectively over a 6-week period. Participants will be received five times: the first four sessions (ie, time 1, time 2, time 3, time 4) occurring at a week’s interval, and a fifth session, corresponding to a follow-up session, occurring 3 weeks after the fourth session (ie, repetition of the first session).

After providing their informed consent, participants will be assigned to the previously randomly determined group (ie, the experimental group receiving the intervention or the control group) using the online tool Research Randomizer.^62^ All participants will be asked to avoid caffeinated beverages within 4 hours before the study, to avoid smoking 2 hours before the study and to avoid consuming any stimulants in general.

Participants will be received at Maisonneuve-Rosemont Hospital (Montreal, Quebec, Canada) and seated in a designated study room. This room provides a controlled, quiet environment with a comfortable seat. Before the first session, participants will complete a sociodemographic and clinical questionnaire. Participants will answer questionnaires assessing subjective variables of interest before and after each session (ie, time 1, time 2, time 3, time 4 and time 5). Physiological measurements will be taken from 10 min before the beginning of the intervention.

Figure 1 displays a schematic representation of the procedure.

**Figure 1 F1:**
[figure not shown]
Graphical representation of the procedure.

### Blinding and allocation concealment

Assignment to either one or the other group being fully automated and realised before the intervention by a team member who is not involved in data collection, outcome assessors will not have any influence on participants’ allocation. Allocation will be concealed until the first meeting with participants. Given the non-pharmacological nature of the study, participants and researchers directly involved in the intervention delivering and outcome assessment cannot be blinded to group allocation. Indeed, the intervention differs according to the condition and technical manipulations are needed from the assessors to display the appropriate virtual content. However, to limit remaining bias, all datasets will be coded to preserve blinding during statistical analysis. Thus, data analysts will remain blinded throughout the study and until the end of analysis.

To further reduce expectancy and performance bias, neutral information will be provided to participants, emphasising that both conditions are credible and that the study aims to evaluate which approach is more effective. Intervention materials will be presented in a standardised format, and all communication with participants will be conducted in a manner that does not suggest preferential expectations regarding one condition over the other.

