## Methods and analysis

### Study design

This study is a preregistered randomised, longitudinal and monocentric project, led at the Hospital Maisonneuve-Rosemont (Montréal, Québec, Canada). This refers to a phase II randomised controlled trial according to the ORBIT (Obesity-Related Behavioral Intervention Trials) model.^49^ The goal of this type of study is to prepare the phase III study, investigating feasibility and acceptability of the study in terms of recruitment and adherence to the protocol and preliminary efficacy. According to the authors of this model, ‘pilot’ randomised trials are considered as a suitable methodology for this phase.

Recruitment of participants will be run from 1 May 2025 to 30 April 2026. Enrolment of participants will be managed by the research assistants responsible for the data collection. This study will evaluate the efficacy of an intervention combining VRH to alleviate pain in patients with hand arthritis. This study will also consider other clinical variables known to influence the experience of pain.

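### Concealment ends at the first meeting although the arms do not differ until session 3, so baseline and early pain ratings may be given with the arm known for no operational reason

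*Protocol article*

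**What the plan says.** Blinding and allocation concealment: the assignment is automated and "realised before the intervention by a team member who is not involved in data collection". The same section then states "Allocation will be concealed until the first meeting with participants". It holds that participants, and the researchers who deliver the intervention and assess outcomes, cannot be blinded, because the intervention differs by condition and "technical manipulations are needed from the assessors to display the appropriate virtual content". The safeguards it lists are neutral information to participants, standardised materials, even-handed communication and blinded data analysts.

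Intervention: in sessions 1 and 2 "participants from both the experimental and control group will not interact with the environment"; both groups watch a beach or forest animation and relax. The arms part only afterwards. "In the control group, sessions 3 and 4 (ie, time 3 and time 4) will consist of the repetition of sessions 1 and 2", while the experimental group moves on to hypnosis, the magic hand exercise and pain manipulation. Session 5 repeats session 1 for everyone.

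Data collection: "After providing their informed consent, participants will be assigned to the previously randomly determined group". Questionnaires are completed before and after each of the five sessions. Study design adds: "Enrolment of participants will be managed by the research assistants responsible for the data collection".

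Primary outcome: a single self-rated 0 to 10 score for current pain in the more painful hand.

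**The concern.** The reason given for not blinding is operational: somebody has to load the right content. That reason has force only when the content differs between arms. For the first two sessions it does not, yet the rule lifts concealment at the first meeting.

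The outcome is a subjective single-item rating. A participant who knows the arm before rating baseline pain may rate it with hope or disappointment, and staff who know the arm may colour the encounter without intending to. A shift at baseline carries into every change measured from it, including the comparison of session 1 with session 5 for which the design repeats the first session. Participants who learn early that they are in the control arm may also leave before treatment has differed at all. Blinded analysis cannot repair a self-report that was already influenced when it was given.

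**Working it through.** The plan gives no figure for this point, so the main check sets its own statements side by side.

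**Step 1. Does showing the content require knowing the arm?** (Intervention section)

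| Session | Control | Experimental | Arm needed to display content? |
|---|---|---|---|
| 1 | beach or forest | beach or forest | No |
| 2 | beach or forest | beach or forest | No |
| 3 | repeat of sessions 1 and 2 | magic hand or pain manipulation | Yes |
| 4 | repeat of sessions 1 and 2 | magic hand or pain manipulation | Yes |
| 5 | repeat of session 1 | repeat of session 1 | No, but the arm is known by then |

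The counterbalancing of beach and forest over sessions 1 and 2 is an ordering separate from the arm, so it does not require the arm to be known either. The arm is first needed at the start of session 3.

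**Step 2. How many ratings precede that point?** (Data collection section)

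- Total: 5 sessions × 2 (before and after) = 10.
- Before any difference in content: 2 sessions × 2 + 1 (before session 3) = 5.
- Share: 5 of 10, including the baseline.

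**Step 3. Is the order of consent, baseline and release fixed?**

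- Data collection places assignment after consent, to a group already drawn.
- Blinding and allocation concealment ends concealment at the first meeting, without placing that moment before or after consent or the baseline questionnaire.
- Study design gives enrolment to the same assistants who collect the data.

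These statements are compatible with release after consent and baseline, but they do not require it.

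**Step 4. What would a later release do to post-randomisation loss?** Inputs from the power section: 98 recruited, 20% total attrition, so 98 × 0.20 = 19.6 lost and 78.4 finishing. The drop-out pattern is not given, so two assumptions are shown.

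- *Even over the four intervals:* 19.6 / 4 = 4.9 per interval. Lost before session 3: 2 × 4.9 = 9.8, leaving 88.2. Later loss: 9.8 / 88.2 = 11.1%.
- *Proportional to time* (gaps of 1, 1, 1 and 3 weeks, 6 in all): lost before session 3: 19.6 × 2/6 = 6.5, leaving 91.5. Later loss: 13.1 / 91.5 = 14.3%.

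These reductions arise only if randomisation itself moves to session 3. If only the opening of the code is delayed, early drop-outs still count as post-randomisation losses, though they occur blind. Delayed opening changes neither the sample size nor alpha nor power.

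**The case against.** The best defence has four parts.

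*Disclosure at session 1 is inferred.* The article does not say outright that participants are told their arm then. The sentence sets the point up to which concealment lasts; the full protocol or the procedure figure, which is not shown here, may give the exact moment. This stands as a limit on the claim: the ratings may be given with the arm known, not that they will be. It does not rescue the reason offered for not blinding, which the Intervention section contradicts for sessions 1 and 2.

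*Safeguards exist.* Neutral information and standardised communication do address expectancy, and having a person outside data collection make the assignment is a genuine protection. Neither keeps the arm hidden during sessions 1 and 2.

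*The main exposure remains.* Ratings after session 3 begins, including follow-up, are unavoidably open, and this is a phase II trial of feasibility and preliminary efficacy. That is true and limits the gain. It is not a reason to give up a blinded baseline that costs little.

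*Some stronger readings go too far.*

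- A reader might infer that consent itself is unblinded and that selective enrolment follows. The Data collection section puts assignment after consent, and nothing says the enrolling assistant holds the code beforehand. It is only a possibility left open by the unclear order.
- A reader might want to pool the ratings before sessions 1 to 3 as a blinded baseline. Those before sessions 2 and 3 follow virtual reality exposure, and the design repeats session 1 at session 5 precisely to compare like with like.
- A reader might credit delayed opening with lower attrition. Only moving randomisation would do that.

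**Conclusion.** The point holds in a limited form. The reason given for lifting concealment at the first meeting does not apply before session 3, so baseline pain and four further assessments, 5 of 10 in total, are avoidably open to expectancy bias and to drop-out informed by the allocation. The order of consent, baseline and release is also not fixed.

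This rests on reading the end of concealment, together with the statement that participants and staff cannot be blinded, as permitting disclosure at the first meeting. The documents give no basis for the direction or size of any resulting bias, and none is claimed. The remaining loss of 11% to 14% instead of 20% is an illustration under two assumed drop-out patterns and applies only if randomisation is moved.

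**What to change.** - State that the allocation stays sealed from participants and from the staff who enrol, deliver and assess until the questionnaires before session 3 are complete, and is opened then.
- Reconcile the Data collection section with the Blinding and allocation concealment section so that release clearly follows both consent and the baseline questionnaire.
- Limit the justification for not blinding to the period from session 3 onward.
- Keep the rating before session 1 as the baseline.

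Cost: a protocol amendment submitted to the ethics committee, and a sentence in the consent information saying that the condition is disclosed at session 3. No extra visits, assessments or staff are needed. Ratings from the start of session 3's content onward remain unblinded.

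Optional: move randomisation itself to that point. This would reduce post-randomisation loss, but it is a design trade-off: about 88 to 91 of the 98 recruited would then be randomised under the two drop-out patterns above.

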### Power analysis and statistical analysis

Quantitative variables will be expressed as mean±SD and categorical variables as frequency and percentages. The impact of the intervention on outcomes of interest will be based on a univariate approach followed by a multivariate approach employing ad hoc model, depending on the structure of the data. Only variables with p<0.20 in the univariate analysis will be considered in the multivariate model. All inferential tests will be two-tailed with a significance level equal to 0.05.

An a priori power analysis was conducted for an analysis of variance (repeated measures, between factors) using the G*Power V.3.1.9.7 software considering current perceived pain as measured with the BPI-SF as main outcome. The effect size *f* was set to 0.25 (medium effect size),^63 64^ the α error risk to 0.05 and the β factor to 0.80. The resulting sample size was calculated as n=82.

As stated in the literature,^65^ an attrition risk should be considered for which an over-recruitment is recommended at time 1 to maintain the required sample size for statistical power. In that sense, a total attrition rate of 20% is expected, leading to recruitment of 98 participants at time 1. Recruitment will be stopped once this targeted sample size is reached. Missing data will be handled by proceeding to multivariable imputation.

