**Methods and analysis:**

This study will be a single-centre randomised clinical trial. Participants will be randomly assigned to one of two conditions: one receiving an intervention combining virtual reality and hypnosis, and the other receiving only virtual reality. The effectiveness of the intervention on current perceived pain before and after the intervention (primary outcome) will be evaluated. Secondary outcomes will include anxiety and depressive symptoms, quality of life, relaxation and fatigue. Exploratory analyses will also be conducted to contribute to the emerging literature by examining physiological variables such as heart rate variability, respiratory rate and electrodermal activity during the intervention, and their relationship with primary and secondary outcomes.

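### The 80% power behind n=82 belongs to an arm comparison averaged over repeated measurements, and does not carry over to a difference that emerges only after hypnosis starts

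*Protocol article*

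**What the plan says.** The section Power analysis and statistical analysis of the protocol article reports: "An a priori power analysis was conducted for an analysis of variance (repeated measures, between factors"), run in G*Power with current pain on the BPI-SF as the main outcome. The effect size f "was set to 0.25 (medium effect size"), with "the α error risk to 0.05 and the β factor to 0.80". The outcome is "The resulting sample size was calculated as n=82". The recruitment target is built on that number: "a total attrition rate of 20% is expected, leading to recruitment of 98 participants at time 1". The number of repeated measurements and their correlation are not given.

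The Intervention section states that in sessions 1 and 2 "participants from both the experimental and control group will not interact with the environment"; everyone watches the same beach or forest scenes. In sessions 3 and 4 the control arm repeats these scenes, while the experimental arm receives hypnosis techniques. Session 5, three weeks later, repeats session 1 in both arms, so that baseline can be compared with the period after the intervention.

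The abstract defines the primary outcome as current pain before and after the intervention. The Objectives section expects lower pain than in the control arm, and a fall from the first to the last treatment session that holds at three weeks.

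**The concern.** In G*Power, the between-factors option for repeated measures tests the group main effect, that is, the arm difference in each patient's mean over all measurements entered. An f of 0.25 with two equal groups therefore means d=0.5 on that mean. The design and the stated aims describe something else: arms treated alike at first, and a difference appearing once hypnosis begins. If sessions before hypnosis are part of the mean, they pull the difference towards zero, and a medium effect after hypnosis is no longer a medium effect on the mean.

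At stake is what the quoted 80% means. Readers will take it as the chance of detecting a medium added effect of hypnosis. If a null result came from an averaged comparison of this kind, it would say much less about the value of hypnosis than the power statement suggests.

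**Working it through.** **Inputs from the article.** Two arms ("Participants will be randomly assigned to one of two conditions"), f=0.25, alpha 0.05 two-sided, power 0.80, N=82.

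**Assumptions.** Equal allocation, one pain score per time point (except in the ten-assessment scenario), equal variances, and one common correlation r between measurements. Here r=0.5 is the base case and 0.3 to 0.7 the range.

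**1. Reproducing 82.** For the between-factors test with m measurements,

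λ = f² · N · m / (1 + (m−1)r), referred to a noncentral F with 1 and N−2 degrees of freedom.

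With m=4 and r=0.5: λ = 0.0625 × 82 × 4 / 2.5 = 8.2, power 0.808. With N=80 power is 0.798, so 82 is the smallest even total that reaches 80%. At r=0.5 other values of m give other totals:

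| m | N for 80% power |
|---|---|
| 2 | 98 |
| 3 | 86 |
| 4 | 82 |
| 5 | 78 |
| 10 | 72 |

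The within-between interaction option at f=0.25 and r=0.5 gives 34 (m=2), 24 (m=4) or 22 (m=5). The 82 is thus a between-factors figure, as the article says. The pair m=4, r=0.5 is the match with a round correlation, but it is inferred. The same total also arises with m=2 and r of 0.25 to 0.27, m=3 and 0.44 to 0.45, m=5 and 0.53 to 0.54, or m=10 and 0.58 to 0.59.

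**2. Dilution.** If d=0.5 holds at k of the m measurements and is zero at the rest, f on the mean is 0.25 × k/m. Power of the between-factors test at N=82:

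| Measurements averaged | f on the mean | r=0.3 | r=0.5 | r=0.7 |
|---|---|---|---|---|
| Times 1-4, effect at 3 and 4 | 0.125 | 37% | 29% | 25% |
| Times 1-5, effect at 3, 4 and 5 | 0.150 | 53% | 41% | 34% |
| Times 1-5, effect at 3 and 4 only | 0.100 | 27% | 21% | 18% |
| Ten pre/post scores, five affected | 0.125 | 45% | 33% | 26% |
| Pre/post scores of sessions 3 and 4, three of four affected | 0.1875 | 68% | 56% | 48% |

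For the first row at r=0.5: λ = 0.015625 × 82 × 4 / 2.5 = 2.05. To keep f=0.25 on the mean of times 1-4, d would have to be 1.0 at times 3 and 4 (0.5 × 4/2). Over times 1-5 with a persisting effect it would be 0.83 (0.5 × 5/3).

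**3. Contrasts that match the aim, N=82, d=0.5.** With residual variance v in units of the single-score variance, λ = 0.0625 × 82 / v = 5.125 / v.

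- Mean of times 3-4, adjusted for mean of times 1-2: v = (1+r)/2 − r²/((1+r)/2), which is 0.512, 0.417 and 0.274.
- Time 4 adjusted for time 1: v = 1−r², which is 0.91, 0.75 and 0.51.
- Unadjusted change from time 1 to time 4: v = 2(1−r), which is 1.4, 1.0 and 0.6.

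| Contrast | r=0.3 | r=0.5 | r=0.7 |
|---|---|---|---|
| Mean of times 3-4 given mean of times 1-2 | 88% | 93% | 99% |
| Time 4 given time 1 | 65% | 73% | 88% |
| Change, time 1 to time 4 | 47% | 61% | 82% |

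**The case against.** The article does not say which measurements entered the calculation. Questionnaires are completed before and after every session, so four measurements need not be times 1-4. They could be the scores around sessions 3 and 4, where dilution is milder (56% at r=0.5). With two measurements, both after hypnosis has begun, there would be no dilution. This stands: every diluted figure is a scenario.

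The article also does not commit to the group main effect as its analysis. That test appears only in the sample-size sentence; the analysis sentence leaves the model to the structure of the data. A reader might infer that the trial will be analysed by a main effect over all sessions and has 29% power. The documents do not support that. What remains is that the only power figure offered is tied to a test that was not shown to fit the stated aim.

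A reader might also infer that no arm difference at all is possible in sessions 1 and 2. Identical content rules out a hypnosis effect there, but the Blinding and allocation concealment section says participants are not blinded, so expectancy could produce some difference. The Objectives section does include a plain between-arm expectation, so a group comparison is not irrelevant; the problem is averaging it over pre-hypnosis sessions.

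Finally, the Study design section describes a phase II trial seeking preliminary efficacy. That lowers the stakes, but the article still claims formal power and derives its recruitment target from it.

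**Conclusion.** The point holds as a mismatch between the powered test and the contrast of interest. The 82 is a between-factors number, and its 80% applies to d=0.5 on the average of whatever measurements were entered. If that average includes pre-hypnosis sessions, the 80% does not carry over to a medium effect that begins with hypnosis. At r=0.5 the scenarios with pre-hypnosis sessions give 21% to 41%. Over all scenarios examined, including the milder one and r from 0.3 to 0.7, the range is about 18% to 68%.

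It would be going too far to conclude that the trial is underpowered. With the same 82 analysed patients, a baseline-adjusted comparison of averaged scores exceeds 80% throughout the range examined, while single-time contrasts may or may not reach it. These results rest on equal allocation, a common correlation and d=0.5 at each affected measurement. Severity: should be fixed.

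**What to change.** Base the power statement on one named primary contrast: the between-arm difference in current pain after hypnosis starts, adjusted for pain before it. The preferred form is the mean of times 3-4 with the mean of times 1-2 as covariate. Say which score within each session is used, how many measurements enter and what correlation is assumed, and restate power at the planned N from the third table of results. Replace the β wording by power (1−β) = 0.80, since a β of 0.80 would literally mean 20% power.

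The change is to text only, uses data already scheduled, and needs no extra patients for the preferred contrast. Its costs are two. If a single time point is kept and the correlation is low, the restated power may fall below 80% (65% to 73% for time 4 given time 1 at r=0.3 to 0.5, lower still for unadjusted change). And times 1-2 follow allocation in unblinded participants, so any expectancy effect on those scores would enter the adjustment; this should be acknowledged.

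### The recruitment target of 98 does not keep the required 82 at the stated 20% attrition: about 78 completers are expected (minor arithmetic correction)

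*Protocol article*

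**What the plan says.** Everything needed is in the Protocol article, section Power analysis and statistical analysis.

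- The base sample size comes from a G*Power calculation for a repeated-measures analysis of variance (between factors) with effect size f = 0.25: "The resulting sample size was calculated as n=82". The error rates are given as "the α error risk to 0.05 and the β factor to 0.80"; the 0.80 is evidently the power, although it is labelled β.
- The reason for recruiting more than 82 is explicit: "over-recruitment is recommended at time 1 to maintain the required sample size for statistical power".
- The allowance follows: "In that sense, a total attrition rate of 20% is expected, leading to recruitment of 98 participants at time 1".
- The target is also the stopping point: "Recruitment will be stopped once this targeted sample size is reached".

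The same paragraph ends by planning multivariable imputation for missing data. The article gives neither the number of repeated measurements nor the correlation used in G*Power.

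**The concern.** Three figures (82 required, 20% lost, 98 recruited) are tied together by a stated purpose, and they cannot all hold. The 98 looks like 20% added to the required number. An attrition rate applies to the people recruited, so the required number has to be divided by the proportion retained.

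At stake is whether the trial, on its own assumptions, ends with the number of completers that it says it needs. Because recruitment stops at 98, the shortfall is built into the target. The article also presents this trial as preparation for a larger phase III trial, so the same inflation method could be carried forward to a setting where it costs more.

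**Working it through.** **Inputs from the article:** required N = 82; attrition 20%; recruitment 98; f = 0.25; two-sided α = 0.05; power 0.80; two groups.

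**Assumed, because not stated:** equal arms; number of measurements m; correlation r between measurements.

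**1. Reproduce the 98.** 82 x (1 + 0.20) = 98.4, which rounds to 98. Dividing by the retained proportion gives 82 / (1 - 0.20) = 102.5, which does not round to 98.

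**2. Expected completers.** 98 x (1 - 0.20) = 78.4, about 78, and 82 - 78 = 4 short.

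**3. Attrition that 98 can absorb.** 1 - 82/98 = 0.163, or 16.3%.

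**4. Target that meets the stated purpose.** 102.5 rounds up to 103, or 104 for two equal arms. Check: 103 x 0.80 = 82.4 and 104 x 0.80 = 83.2.

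Steps 1 to 4 use only figures printed in the article, apart from equal arms for the 104.

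**5. Reproduce the 82.** For a between-groups effect in a repeated-measures ANOVA, the noncentrality is λ = f² N m / (1 + (m - 1) r), referred to an F distribution with 1 and N - 2 degrees of freedom. With r = 0.5, the smallest even N that reaches 80% power is:

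| m | N |
|---|---|
| 2 | 98 |
| 3 | 86 |
| 4 | 82 |
| 5 | 78 |

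So m = 4 with r = 0.5 returns the article's 82. This is an inference about the inputs. The article does not state them.

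**6. Power among completers, m = 4 and r = 0.5.** Here λ = 0.0625 x N x 4 / 2.5 = 0.1 N.

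| N | λ | Power |
|---|---|---|
| 78 | 7.8 | 0.787 |
| 80 | 8.0 | 0.798 |
| 82 | 8.2 | 0.808 |
| 98 | 9.8 | 0.873 |

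The loss from 82 to 78 is 0.808 - 0.787 = 0.021, about two percentage points.

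**7. Sensitivity to the assumed inputs.** Other pairs also return 82. At N = 78 they give:

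| m | r | λ at N = 78 | Power |
|---|---|---|---|
| 3 | 0.44 | 14.625 / 1.88 = 7.78 | 0.786 |
| 3 | 0.45 | 14.625 / 1.90 = 7.70 | 0.782 |
| 5 | 0.53 | 24.375 / 3.12 = 7.81 | 0.788 |
| 5 | 0.54 | 24.375 / 3.16 = 7.71 | 0.783 |

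The pairs that fit the stated 82 therefore put 78 completers at about 78% to 79%. With m = 5 and r = 0.5, N = 78 gives 0.804, but those inputs return a required N of 78 and so do not fit the article.

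**The case against.** **The planned analysis is not limited to completers.** A reader might infer that the trial will finish below its stated 80% power. The article does not support that. It plans multivariable imputation, and the "Data collection" section has questionnaires before and after each of five sessions. Someone lost before the follow-up session may already have contributed up to four sessions, and a between-factors test uses the average over measurements, so partial data carry information. Under the inputs assumed above, the effective power would plausibly lie between that of 78 and that of 98 participants, 0.787 to 0.873. This objection stands as a limit on the consequence. It does not rescue the sentence, because the article justifies over-recruitment by keeping the required number after attrition, and imputation does not turn 78 completers into 82.

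**The power figures rest on inputs that the article does not give.** A reader might take m = 4 and r = 0.5 for the plan's own settings. They are assumptions, and four measurements do not match the five sessions. This also stands. The direction survives, since each pair checked that returns 82 puts 78 slightly below 80%, but the exact figure must come from the sponsor's G*Power record.

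**The shortfall is small for this kind of trial.** The article describes a phase II, pilot-type trial concerned with feasibility, acceptability and preliminary efficacy. The 20% and the f of 0.25 are round planning values, and a change of 20 - 16.3 = 3.7 points in attrition closes the gap. This stands, and it is why the point is minor.

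**The 20% might have been meant as a recruitment margin.** The text calls it an attrition rate and derives 98 from it. If a margin was meant, the sentence is worded wrongly and still needs correcting.

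**Conclusion.** The sentence is wrong as written, and the error is minor. At the stated 20% attrition, 98 recruits are expected to give about 78 completers instead of 82, and 98 preserves 82 only up to 16.3% attrition. This part rests on no unstated input.

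The effect on power is about two points among completers (about 79% against 81%), assuming m = 4, r = 0.5 and equal arms. The other input pairs checked that reproduce 82 give about 78% to 79%. The conclusion covers the number of completers. It does not show that the final analysis, with imputation and partial data, will be underpowered, and nothing here puts the trial's validity in question.

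**What to change.** Correct the attrition sentence in the section Power analysis and statistical analysis in one of these ways:

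- **Keep 98 and restate the expectation.** For example: with 98 recruited and 20% attrition, about 78 participants are expected to complete. Add the corresponding completer power, read from the sponsor's own G*Power inputs; the 79% above depends on assumed inputs and should not be copied in.
- **Keep 98 and restate the tolerance.** For example: recruiting 98 retains 82 completers provided that attrition does not exceed about 16%.
- **Raise the target, if the sponsor wants 82 completers at 20% attrition.** The target becomes 103, or 104 for equal arms, and the recruitment stop moves with it.

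Either of the first two costs one sentence; the stated expectation becomes slightly less favourable. The third adds 103 - 98 = 5 or 104 - 98 = 6 participants. The "Feasibility" section reports more than 3200 patients on a waiting list, so availability is no evident barrier.
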